The second objective is to determine the feasibility of a 12-week community-based post-TKA multimodal program and collect preliminary data with respect to the efficacy of the combination of different exercise components (i.e., including evidence-based strengthening and balancing exercises, and Tai Chi) in improving balance and physical functioning in post-TKA patients as compared to usual postoperative care. A third group of asymptomatic controls will be included to investigate whether the postoperative rehabilitation program can restore balance and mobility of TKA patients more akin to asymptomatic individuals. It is hypothesized that the multifaceted exercises is a feasible intervention for post-TKA patients, and those in the intervention group will demonstrate better physical function and balance control than patients receiving usual postoperative care.

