### Sample size

No formal sample size calculation was performed for this feasibility study. However, a minimum sample size for a pilot study to evaluate the feasibility of conducting a full-scale trial is suggested to be 50 per study [18, 19]. A total of 78 patients (26 per arm) were deemed an appropriate sample size for this trial to estimate the recruitment and retention rates and explore the acceptability of the intervention.

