## Statistical analysis

The data regarding the feasibility, acceptability, adverse events, intervention adherence, missing data rates and data completion rates will be summarized using descriptive statistics. The experience and perception of participants toward the RCT solicited from semi-structured interviews will be analyzed by framework analysis [39, 40].

To determine the feasibility of studying the proposed outcomes in a definitive trial, inferential analysis will be conducted at 95% confidence intervals, and the significance level will be set at 0.05. The effect size of each intervention outcome will also be estimated. Descriptive statistics will be used to summarize patient demographic data. Baseline demographic and clinical variables (such as BMI, medication, number of comorbidities) in the three groups will be compared using analyses of variance (ANOVAs) and Kruskal-Wallis tests for parametric and nonparametric data, respectively. Any baseline variables that show significant between-group differences will be used as covariates in subsequent between-group analyses of outcome measures. Separate two-way repeated measures analyses of covariate (ANCOVA) or ANOVA will be used to evaluate within- and between-group changes in various outcome measures at several follow-up time points (i.e., 6, 12, 24, and 52 weeks after TKA for TKA patients, and 12 and 24 weeks after baseline for asymptomatic controls) in the three groups. Statistical analyses will be conducted using SPSS version 21.0 (IBM Corporation, NY, USA). Following the intention-to-treat principle, between-group differences in primary and secondary continuous outcomes in all randomized participants at different time points will be analyzed. Per-protocol analysis will also be reported for all planned outcomes in participants who strictly followed the protocol.

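### The only outcome model the plan specifies is a three-group repeated-measures ANOVA/ANCOVA that includes non-randomised asymptomatic controls; its F tests cannot test intervention versus usual care, and the promised comparison of randomised participants is tied to no model

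*Protocol article*

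**What the plan says.** All references are to the protocol article.

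- **Hypothesis.** The Background states the efficacy hypothesis as one comparison: "those in the intervention group will demonstrate better physical function and balance control than patients receiving usual postoperative care". The Discussion repeats it.
- **Model.** Statistical analysis specifies one inferential model for outcomes: "Separate two-way repeated measures analyses of covariate (ANCOVA) or ANOVA will be used to evaluate within- and between-group changes in various outcome measures". The follow-up times listed for it are weeks 6, 12, 24 and 52 after surgery for the operated patients and "12 and 24 weeks after baseline for asymptomatic controls) in the three groups". On inference, "the significance level will be set at 0.05".
- **Randomised comparison.** Under intention to treat, the same section adds that "between-group differences in primary and secondary continuous outcomes in all randomized participants at different time points will be analyzed". It names no model, contrast or visit for this.
- **Who is randomised, and when.** Only the two knee-replacement arms are randomised, after the 12-week postoperative assessment (Randomization and allocation). The asymptomatic controls are a non-randomised cohort (Inclusion and exclusion criteria).
- **Size.** "No formal sample size calculation was performed for this feasibility study"; "A total of 78 patients (26 per arm) were deemed an appropriate sample size for this trial".
- **Aim of the third group.** The controls serve a separate question: whether the programme brings patients' balance and mobility closer to those of asymptomatic people (Background, Study design, Discussion).

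**The concern.** A group or group-by-time F test over three groups has a null hypothesis that all three groups are alike, or change alike. The protocol itself expects that null to be false for reasons unrelated to the programme. Its Discussion says that patients one year after surgery still walk and balance worse than matched asymptomatic people, and that surgery improves pain and function. Both operated arms can therefore differ from the controls, and change relative to them, while being identical to each other.

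Two features of timing add to this. Weeks 6 and 12 come before randomisation, so arm differences at those visits cannot be programme effects, yet they enter the model as follow-up. The controls also lack some of the patients' visits, so a three-group fit must leave out at least one post-randomisation visit.

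At stake is what a significant result would mean. If the omnibus F were taken as a signal about the programme, a null programme could look promising for the definitive trial.

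**Working it through.** **Plan's own figures.** 3 × 26 = 78 and 2 × 26 = 52, as stated. The documents give no effect size or SD, so there is no power figure to reproduce.

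**Inputs.** From the protocol: 26 per group and α = 0.05. Assumed, because the documents give no SDs: outcome SD 1 at each visit; within-person correlation ρ = 0.6; both operated arms identical (no programme effect); controls better by *a* SD at week 12 and *b* SD at week 52, with *b* = *a*/2. These two follow-up visits are common to all groups under the schedule given in most sections.

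**Formulas.** With two visits, each F test is a one-way ANOVA on a per-person summary, with 2 and 75 degrees of freedom and a 5% critical value of 3.119.

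- Group-by-time uses week 52 minus week 12: variance 2(1 − ρ) = 0.8, gap *g* = *a* − *b*.
- Group uses the two-visit mean: variance (1 + ρ)/2 = 0.8, gap *g* = (*a* + *b*)/2.
- With two equal groups and one shifted by *g*, the noncentrality is λ = 26 × (2/3) × *g*² / 0.8.

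**Results with zero programme effect.**

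| Gap wk 12, wk 52 (SD) | Group-by-time: *g*, λ, P(reject) | Group: *g*, λ, P(reject) |
|---|---|---|
| 0.5, 0.25 | 0.25, 1.354, 16.0% | 0.375, 3.047, 31.5% |
| 1, 0.5 | 0.5, 5.417, 52.1% | 0.75, 12.188, 87.5% |
| 2, 1 | 1.0, 21.667, 98.8% | 1.5, 48.75, about 100% |

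Simulation with 4,000 trials per scenario agrees: 15.8% and 32.0%, 52.2% and 87.2%, 98.7% and 100%. With no gap it gives 4.9% and 5.1%. A two-arm ANCOVA at week 52 adjusted for week 12 rejects in 4.3–5.3% throughout.

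**Sensitivity.** With baseline, week 12 and week 52 in the model, controls flat, and both operated arms recovering 60% of a baseline deficit by week 52, group-by-time rejects in 11–22% for a 0.5 SD deficit and 37–74% for 1 SD, over ρ from 0.3 to 0.7. Even a constant gap of 0.2 SD of the person mean gives 10.4% for the group test (λ = 26 × (2/3) × 0.04 = 0.693). The same tests restricted to the two randomised arms stay near 5% in every scenario.

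**Visits.** The sections do not agree on when controls are seen:

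- Statistical analysis: 12 and 24 weeks after baseline.
- Abstract, Study design, Untreated asymptomatic controls, Secondary endpoints, the note to Table 1, and Remote monitoring of physical activity: 12 and 52 weeks.

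On the 12/52 schedule a three-group fit omits week 24, when supervised training ends. On the 12/24 schedule it omits week 52. On neither do controls have a week-6 visit, so a complete-case fit over all patient visits would drop every control.

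**The case against.** The strongest reply is that the randomised comparison is already in the plan. The intention-to-treat sentence covers all randomised participants, and since only two arms are randomised, that can only be intervention versus usual care. This stands. A reader might infer that the plan contains no such comparison, and the text does not support that. What the sentence lacks is any link to a model; the one model specified is the three-group one.

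Second, the three-group comparison has its own stated aim, the benchmark against asymptomatic people. This also stands: a model with controls is relevant to that question. It remains the wrong test for the efficacy hypothesis.

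Third, a reader might take the rejection rates above as the trial's false-positive rate. They are not. In those scenarios the controls really differ, so the omnibus test rejects correctly. The rejections become false positives only if the F test is read as evidence for the programme, which the protocol never says it will do. The risk is that nothing in the text prevents that reading.

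Fourth, a condensed article may leave post hoc contrasts to a fuller document. That is fair for the missing detail, but the three-group model is stated here and is the point at issue.

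Finally, feasibility is the primary endpoint and the trial is declared not powered for efficacy. This lowers the severity. It does not make the three-group F informative about the programme.

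**Conclusion.** The point holds with moderate severity. The three-group omnibus F tests cannot test intervention versus usual care, and the promised comparison of randomised participants is not connected to a model that can. This follows from the structure of the test and needs no assumption.

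The size does rest on assumptions. For gaps of 0.5 to 1 SD halving by week 52, with ρ = 0.6, the omnibus tests reject in about 16–52% (group-by-time) and 31–88% (group) of trials with no programme effect, against about 5% for a two-arm ANCOVA. Smaller gaps give less and larger gaps more; with no gap the rate is 5%.

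The pilot's stated use of KOOS, an SD for the next sample-size calculation, does not depend on these F tests, and no progression decision is tied to them.

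**What to change.** State in Statistical analysis that:

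- programme effects are estimated in the two randomised arms only, as intervention minus usual care at the post-randomisation visits (weeks 24 and 52), by ANCOVA or a mixed model adjusted for the week-12 value, with 95% CIs;
- this is the analysis meant by the intention-to-treat sentence;
- the asymptomatic group is analysed separately as a benchmark, and the three-group F tests are not used to judge the programme.

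Reconcile the controls' visit schedule between Statistical analysis and the other sections.

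The key outcome and decisive visit remain the investigators' choice. The protocol lists two candidate primary outcomes for the definitive trial (KOOS and trips/falls), and home exercise continues to week 36, so neither choice follows from the text.

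**Cost.** Wording only: no new patients, visits or data. The two-arm result will look less significant than the three-group F. Before covariate adjustment, at 26 per arm and two-sided 0.05, power for a true 0.5 SD difference is about 44% (0.5/√(2/26) = 1.80; 1.80 − 1.96 = −0.16). For 0.8 SD it is about 82% (2.88 − 1.96 = 0.92). That is an honest picture of what this pilot can show, and a reason to report estimates with intervals.

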### Randomization and allocation

Upon completion of the 12-week post-operation assessments, TKA participants will be randomized into either the intervention or the usual care group. Permuted blocks using a computer-generated random number schedule will be used to determine the randomization order. Group assignment will be concealed in sealed sequentially numbered opaque envelopes and administered by a research assistant at The Hong Kong Polytechnic University not involved in the study. In addition, various methods will be employed to keep participant data confidential and secure including using password-protected files, limiting access to only those on the study team who require identifiable data, and using de-identified data when possible.

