#### Untreated asymptomatic controls

To minimize the number of physical assessments for untreated asymptomatic controls, this group will undergo only three clinical assessments: at baseline and at 12 and 52 weeks after baseline (Fig. 1). Participants will be given a total possible compensation of $150 supermarket coupons only after the completion of 3 assessments.

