#### Rate of recruitment and rate of retention

The recruitment rate will be calculated as the percentage of people who were screened for their eligibility for participating in the study and subsequently provided informed consent. The attrition rate will be calculated as the percentage of those recruited who did not complete reassessments at subsequent follow-ups. The recruitment and attrition rates will be monitored on a monthly basis to determine the presence of any specific trends. The recruitment rate (all potential participants), retention and attrition rates (all randomized participants), and completion rates (all enrolled participants) will be assessed at the end of study. Reasons for ineligibility and/or non-recruitment of eligible patients will be recorded and grouped into categories. Adverse events in all groups will be monitored, recorded, managed, and followed up. Participants will be given information regarding the procedure for reporting or handling of adverse events (e.g., a dedicated phone line for contacting the research team). All participants will have the right to withdraw from the study at any stage. The reasons for withdrawal will be documented and any data already collected from the participant will not be analyzed.

For participants who need to postpone their surgery after the baseline assessments, they will be reassessed 1 week before the rescheduled surgery. Participants who need to cancel their surgery after the baseline assessments will be treated as dropout cases and the corresponding reasons for non-participation will be documented. This procedure will enable the estimation of the recruitment rate and the sample size for the definitive trial.

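### The repeated-measures ANOVA/ANCOVA named in the plan keeps only participants with every scheduled visit, so it cannot deliver the promised analysis of all randomized participants; the controls' visit list is also wrong

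*Protocol article*

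**What the plan says.** The Statistical analysis section of the protocol article names one model for the outcome measures: "Separate two-way repeated measures analyses of covariate (ANCOVA) or ANOVA will be used to evaluate within- and between-group changes in various outcome measures". The time points follow in brackets: "6, 12, 24, and 52 weeks after TKA for TKA patients, and 12 and 24 weeks after baseline for asymptomatic controls". The software is SPSS version 21.0.

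The same paragraph sets the population: "Following the intention-to-treat principle, between-group differences in primary and secondary continuous outcomes in all randomized participants at different time points will be analyzed". On incomplete data, the section says only that "missing data rates and data completion rates will be summarized using descriptive statistics".

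Three other places bear on the point:

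- **Randomization and allocation:** "Upon completion of the 12-week post-operation assessments, TKA participants will be randomized into either the intervention or the usual care group". Weeks 24 and 52 are therefore the only visits after randomization.
- **Untreated asymptomatic controls:** "this group will undergo only three clinical assessments: at baseline and at 12 and 52 weeks after baseline".
- **Table 1:** most outcomes are measured at baseline and at all four follow-ups. Activity monitoring is not done at week 6, and global change is rated only at weeks 24 and 52.

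**The concern.** Classical two-way repeated-measures ANOVA or ANCOVA needs one complete row per person. Run in the usual way in SPSS, it deletes a participant who lacks any of the visits in the model. The named method and the named population therefore agree only if all 52 randomized participants attend every visit. The plan does not expect that: it will report missing-data rates, and estimating attrition is one purpose of the pilot.

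Two cases show the effect. Someone seen at week 24 but not at week 52 contributes nothing to the week-24 contrast. Someone who missed only week 6, which comes before randomization, contributes nothing to either post-randomization contrast.

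At stake are the precision and possibly the direction of the effect sizes that the section says will be estimated to judge the outcomes for a definitive trial. They would describe completers while being labelled intention-to-treat.

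The three-group comparison has a second problem. The section lists a 24-week follow-up for the controls, which the schedule does not contain, and omits the 52-week follow-up, which it does.

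**Working it through.** **Inputs.** From the article: 52 randomized, 26 per arm; follow-up at weeks 6, 12, 24 and 52; randomization after the week-12 assessment. Week 12 should therefore be present for everyone randomized, and the visits that can be missing are weeks 6, 24 and 52. The article gives no miss rate, effect size or power calculation, so there is no stated figure to reproduce. Assumption: each of the three visits is missed independently with probability p = 3%, 5% or 10%.

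**Participants deleted**, for an outcome measured at all visits: 1 − (1 − p)³.

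- p = 0.03: 1 − 0.97³ = 8.7%; × 52 = 4.5, about 5 people
- p = 0.05: 1 − 0.95³ = 14.3%; × 52 = 7.4, about 7 people
- p = 0.10: 1 − 0.90³ = 27.1%; × 52 = 14.1, about 14 people

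For activity monitoring and global change, which have no week-6 measurement, the exponent is 2: 5.9%, 9.8% and 19.0%, or about 3, 5 and 10 people.

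**Precision at week 24.** Complete cases per arm number 26(1 − p)³, while people seen at week 24 number 26(1 − p). The ratio of standard errors is √[(1 − p)/(1 − p)³] = 1/(1 − p), which is 1.03, 1.05 and 1.11. At p = 10%, the 95% CI half-width in SD units, 1.96 × √(2/n), is 0.64 with complete cases (n = 19.0 per arm) and 0.57 with everyone seen at week 24 (n = 23.4).

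**Bias, illustration only.** Simulation of 20,000 trials with 26 per arm, correlation 0.6 between visits and a true difference of 0.50 SD. In the exercise arm 21% miss week 52, more often those with poor week-24 scores (logistic slope per SD as shown). In usual care 10% miss it at random. Average week-24 difference among complete cases:

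| Missingness in the exercise arm | Complete cases | Everyone seen at week 24 |
|---|---|---|
| Random (slope 0) | 0.50 | 0.50 |
| Slope 0.5 | 0.60 | 0.50 |
| Slope 1 | 0.68 | 0.50 |
| Slope 2 | about 0.77 | 0.50 |
| Slope 1, same mechanism in both arms | 0.50 | 0.50 |

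**Control visits, side by side.** Statistical analysis: 12 and 24 weeks after baseline. Study design, Untreated asymptomatic controls, Secondary endpoints, Remote monitoring of physical activity and the note to Table 1: 12 and 52 weeks. There are no 24-week control data, so the three-group comparison cannot be run on the visits listed.

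**The case against.** The strongest reply is that the article never says incomplete participants are dropped. An ANOVA after imputation would satisfy both sentences, and imputation detail is commonly left to an analysis plan, which is not shown. This stands in part: such a plan could repair the matter. But the point is not that detail is absent. The article itself fixes a method and a population that do not fit together, and following its text yields a completer analysis.

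Several stronger readings are tempting and are not supported:

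- **All 26 controls (a third of 78) are lost by design.** A reader might infer this from a model over weeks 6, 12, 24 and 52 in three groups. The section gives controls their own visit list, so a four-visit model for them is not shown to be planned. What is shown is that their list conflicts with the schedule.
- **A missed visit removes a person from the whole analysis.** Models are separate for each outcome. A missed week 6 leaves activity monitoring and global change untouched.
- **The KOOS standard deviation for the definitive trial would come from completers.** The section on sample size for the future trial does not tie the SD to the ANOVA sample; it can be taken from all values at a visit.
- **The effect will be inflated.** That requires selective missingness concentrated in one arm. Nothing in the article shows this will occur.

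There is also some overlap with a separate rule under Rate of recruitment and rate of retention: "The reasons for withdrawal will be documented and any data already collected from the participant will not be analyzed". Some people who stop attending would be excluded by that rule whatever the model. The deletion described here also affects participants who remain in the study and miss a visit.

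**Conclusion.** The concern holds as a mismatch between the stated population and the only stated model. For an outcome measured at all visits, a randomized participant who misses week 6, 24 or 52 is dropped from every time-point contrast in that outcome's model. The loss is about 5, 7 or 14 of 52, with a week-24 standard error 3%, 5% or 11% larger, under assumed independent miss rates of 3%, 5% or 10% per visit. Bias is a possibility and not a prediction: illustratively 0.60 to 0.77 SD against a true 0.50 if missingness is selective in one arm, and none if it is random or equally selective in both.

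The control visit list is a separate, plain inconsistency that rests on no assumption.

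The consequences are moderate. The primary endpoint is feasibility and acceptability, summarised descriptively, and the trial is not powered for efficacy. The change should be made, but the trial's main purpose does not depend on it.

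**What to change.** For the two randomized arms, replace the repeated-measures ANOVA/ANCOVA with a linear mixed model for repeated measures (SPSS MIXED, REML). Use all available week-24 and week-52 values as outcomes and pre-randomization values (baseline or week 12) as covariates. Report the between-arm contrast at each visit with its 95% CI. Keep the complete-case ANOVA as a sensitivity analysis.

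Compare with the asymptomatic controls in a separate model at the visits both groups have (baseline, 12 and 52 weeks), and correct the controls' follow-up times in the Statistical analysis section to match the schedule.

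Under the same assumed miss rates, a participant contributes no outcome only if both weeks 24 and 52 are missed. At p = 10% that is 0.10² = 1% of 52, or about half a person.

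The cost is a change of wording and slightly more analysis work, with no further data or participants. The model relies on data being missing at random, which should be stated. The feasibility endpoints do not change.

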## Methods

### Study design

This is a single-blinded 2-arm RCT. TKA participants will be randomized to either a 12-week community-based rehabilitation program starting at 12 weeks after TKA, or usual postoperative care without outpatient physiotherapy. A third group of asymptomatic controls will be recruited to provide comparisons at various time points (Fig. 1). A third group of asymptomatic controls will be recruited to investigate whether the postoperative rehabilitation program can restore balance and mobility of TKA patients to the levels found in asymptomatic individuals (Fig. 1). All post-TKA participants will undergo five clinical assessments: 1 week before TKA, and at 6, 12, 24, and 52 weeks after TKA. Two orthopedic surgeons will use a standard parapatellar approach. Two common prosthesis designs (posterior stabilized and medial pivot) will be used in TKA surgery. Previous research has reported no significant differences in self-reported and physical performance outcomes between these prostheses 12 months after TKA [16]. In addition, the untreated asymptomatic controls will be assessed at baseline, and 12 and 52 weeks from baseline. This study protocol has been approved by the Human Research Ethics Committees at The Hong Kong Polytechnic University (HSEARS20171225001) and the Institutional Review Boards of two hospitals (UW 18-452) and has been prospectively registered on clinicaltrials.gov (identifier number: NCT03615638). The protocol has been developed in accordance with Good Clinical Practice, Standard Protocol Items: Recommendation for Interventional Trials (SPIRIT) (see Additional file 1 SPIRIT 2013 checklist). The Human Research Ethics Committees review all study activities annually including ethical conduct, regulatory compliance, and recruitment and retention and can initiate an independent study audit at any time. The investigator team meets biweekly to discuss enrolment targets and treatment fidelity. The study coordinator is responsible for ensuring that data is complete and monitoring study progress including sufficient recruitment and retention. Adverse events across conditions will be reviewed annually; issues with intervention delivery and other unintended consequences of either intervention are discussed during regular supervision meetings. Significant protocol modifications will be approved by relevant Institutional Review Boards and will be reported to relevant parties (e.g., ClinicalTrials.gov) in a timely manner. All participants have the option of discontinuing their participation in the study at any time, and this is indicated in the consent forms. Adverse events will be reported immediately to the principal investigator, tracked, and responded to according to regulatory guidelines. There are no criteria for the modification of the study interventions. As harm from this type of study is rare, there are no provisions in place for ancillary, post-trial, or compensation for study-related harms.

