#### Number of trips/falls

The number of trips, falls, and fall-related injuries in the 12 months before baseline will be documented. During the follow-up, trips/ falls will be recorded using a trip/fall diary.

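### Weeks 6 and 12 precede randomisation but enter the between-group model as follow-up outcomes, and the week-12 value is not used as the pre-treatment reference

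*Protocol article*

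**What the plan says.** Study design in the protocol article schedules five assessments for the surgical patients: "1 week before TKA, and at 6, 12, 24, and 52 weeks after TKA". It describes the intervention as a "12-week community-based rehabilitation program starting at 12 weeks after TKA". Randomization and allocation fixes the order of events: "Upon completion of the 12-week post-operation assessments, TKA participants will be randomized into either the intervention or the usual care group".

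Statistical analysis names the method: "Separate two-way repeated measures analyses of covariate (ANCOVA) or ANOVA will be used". The purpose and the visits given for these models are as follows: "evaluate within- and between-group changes in various outcome measures at several follow-up time points (i.e., 6, 12, 24, and 52 weeks after TKA". Nothing there separates the visits before allocation from those after it.

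The same section adds, under the intention-to-treat principle, that "between-group differences in primary and secondary continuous outcomes in all randomized participants at different time points will be analyzed". Its covariate rule is data-driven: "Any baseline variables that show significant between-group differences will be used as covariates in subsequent between-group analyses of outcome measures". Secondary endpoints places the surgical patients' baseline one week before the operation. The week-12 measurement therefore appears in the analysis only as an outcome.

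**The concern.** Weeks 6 and 12 fall before allocation. Any difference between the two arms at those visits is chance. Listing them as follow-up levels beside weeks 24 and 52 has three consequences.

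- The term that answers the randomised question is left open. The candidate terms in a two-way model do not estimate the same quantity.
- Two of the four visit-specific comparisons between arms cannot reflect treatment, so a significant result there would be a false lead.
- The last measurement before treatment, usually a strong predictor of later values, is not used to sharpen the comparison. The baseline that the covariate rule refers to lies about 13 weeks before randomisation (1 week before surgery plus 12 after), with the operation in between.

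The trial is a pilot with feasibility as its primary endpoint. Even so, the section commits to tests at 0.05, to 95% confidence intervals and to an effect size for each outcome, so those effect sizes should describe the randomised comparison.

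**Working it through.** **Inputs from the protocol article.** There are 26 patients per randomised arm (Abstract; Sample size). The model visits are weeks 6, 12, 24 and 52 (Statistical analysis). Randomisation follows the week-12 visit. The article states no power, effect size, SD or between-visit correlation, so there is no figure of its own to reproduce.

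**Assumptions.** The outcome SD is 1 at every visit. The correlation r between any two visits is the same, taken as 0.5 to 0.6 with a wider range of 0.3 to 0.7. Data are complete.

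**Step 1: what each term estimates.** The expected differences between arms at weeks 6, 12, 24 and 52 are 0, 0, d24 and d52.

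- Group main effect over four visits: (0 + 0 + d24 + d52)/4 = (d24 + d52)/4.
- Mean effect after randomisation: (d24 + d52)/2.
- Ratio: exactly 1/2, whatever d24 and d52 are. If the pre-operative visit were also a level, the main effect would be (d24 + d52)/5, a ratio of 0.4.
- Group-by-time contrast (mean of weeks 24 and 52 minus mean of weeks 6 and 12): (d24 + d52)/2, undiluted.
- Differences at week 24 and at week 52: d24 and d52, undiluted.

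A simulation of 20,000 trials with d24 = d52 = 0.5 SD and r = 0.5 gave 0.251 for the main effect, 0.501 for the week-24 difference and 0.500 for the contrast.

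**Step 2: precision at a single visit.** The standard error of the week-24 difference is √(2v/26), where v is the residual variance.

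- Unadjusted, v = 1: √(2/26) = 0.277 SD.
- Adjusted for week 12, v = 1 − r²:
  - r = 0.5: √(2 × 0.75/26) = 0.240 SD
  - r = 0.6: √(2 × 0.64/26) = 0.222 SD
  - r = 0.3: √(2 × 0.91/26) = 0.265 SD
  - r = 0.7: √(2 × 0.51/26) = 0.198 SD

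For r of 0.5 to 0.6, adjustment shortens the interval by 1 − √0.75 = 13% to 1 − √0.64 = 20%.

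**Step 3: the adjusted analysis against the best use of the planned model.** The table gives per-patient variances for estimating the mean effect over weeks 24 and 52.

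| Estimator | Formula | r = 0.3 | r = 0.5 | r = 0.6 |
|---|---|---|---|---|
| Weeks 24 and 52, unadjusted | (1 + r)/2 | 0.65 | 0.75 | 0.80 |
| Post-minus-pre contrast | 1 − r | 0.70 | 0.50 | 0.40 |
| Adjusted for week 12 | (1 + r)/2 − r² | 0.56 | 0.50 | 0.44 |
| Adjusted for mean of weeks 6 and 12 | (1 + r)/2 − 2r²/(1 + r) | 0.51 | 0.42 | 0.35 |

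The contrast and the week-12 adjustment are equal at r = 0.5. The contrast is slightly better at 0.6 and worse at 0.3. Using week 6 as well improves on both at all three correlations.

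**Step 4: what is at stake in the choice of term.** With 26 per arm, an assumed effect of 0.5 SD at both later visits, r = 0.5 and two-sided 0.05 (normal approximation), power is:

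- 21% for the four-visit main effect
- 55% for weeks 24 and 52 unadjusted
- 72% for the contrast
- 72% for weeks 24 and 52 adjusted for week 12

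**The case against.** The strongest reply is that the plan never makes the group main effect its treatment estimate. It speaks of changes within and between groups and also plans arm differences at separate time points. A reader might infer from the visit list that the treatment effect will be halved. The documents do not support that, because halving occurs only if an analyst reports a term that the plan does not name. This part of the reply stands.

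It also stands that the planned model, used through its post-minus-pre contrast, gives an undiluted estimate about as precise as the week-12 adjustment. Weeks 6 and 12 have a proper place too: they describe recovery within groups, and week 12 is a visit shared with the asymptomatic controls.

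The effect on the definitive trial is limited. What the article explicitly carries forward is the SD of the KOOS (Sample size estimation for the future definitive trial) and the attrition rate (Primary endpoint). An SD not conditioned on the pre-treatment value makes a later sample size larger, which is conservative.

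A reader might extend the criticism to falls, since "During the follow-up, trips/ falls will be recorded using a trip/fall diary" could be taken to start at surgery and so count about 12 weeks before randomisation. The text gives no start date for the diary. The intention-to-treat comparison is confined to continuous outcomes, so ANOVA is not clearly prescribed for fall counts. That extension is not supported.

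What the reply does not remove is the mismatch itself. The plan lists pre-randomisation visits as follow-up outcomes, leaves open terms that differ by a factor of two, and gives the week-12 value no role as reference.

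**Conclusion.** The point holds as a moderate one. The visit list in Statistical analysis conflicts with the time of randomisation, and this follows from the text without any assumption. The factor of one half is exact but conditional: it applies to the four-visit group main effect only, and not to the group-by-time contrast or to the differences at weeks 24 and 52. The unadjusted visit-specific differences lose precision: 0.277 SD against 0.240 to 0.222 SD at week 24, given 26 per arm, equal correlation of 0.5 to 0.6 and no dropout. The power figures also rest on an assumed effect of 0.5 SD and show only how far the candidate terms diverge. A higher grade is not warranted for a pilot whose primary endpoint is feasibility.

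**What to change.** In Statistical analysis, for the two randomised arms:

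1. State that the pre-operative, week-6 and week-12 visits precede randomisation, and make weeks 24 and 52 the only outcome visits.
2. Prespecify the week-12 value of the same measure as a covariate, whether or not the arms differ on it. The week-6 value may be added where it is collected; Table 1 has no week-6 activity monitoring.
3. Report the adjusted arm difference and effect size with 95% CI at week 24 and at week 52, and name these as the randomised comparison.
4. Keep the pre-operative, week-6 and week-12 values for describing recovery within groups and for the comparison with asymptomatic controls.

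The cost is protocol or SAP wording only. Table 1 already schedules the repeated outcome measures at week 12, so no visit or measurement is added. The global impression of change is not collected before week 24 and would be compared without this covariate.
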